### Sample size calculation and statistical analysis

#### Sample size

We present here our power analysis for the primary outcome only. Since this is a novel therapy, we used the data from a previous non-controlled pilot study on treatment-resistant MDD in senior patients [18] to calculate the power. The primary outcome measure is the categorical classification of response; we define the treatment response as a 50% or greater reduction in HAM-D-24 scores following treatments. From a previous proof of concept study [18], the response rate in the tVNS group is 39%; assuming a 20% dropout rate, with 60 patient in each group, we will have 80% power to detect a difference of 25% or greater in response rate between the tVNS and the sham tVNS group based on a chi square test at a 0.05 significance level.

#### Statistical analysis

In this study, the primary outcome measure is the categorical classification of treatment response. We define the treatment response as a 50% or greater reduction in HAM-D-24 scores following treatments. Response rates across the two groups will be compared with the chi square (*x*^2^) test.

Additionally, we will also use the HAM-D-24 score as continuous variable and apply a regression model to compare the different between two treatment groups. More specifically, in the model, the dependent variable is post-treatment HAM-D-24 score, the independent variable is treatment mode (tVNS versus sham tVNS), and covariances will include pre-treatment HAM score, age and gender. Similar analyses will also be performed in other clinical and physiological outcome measurements.

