**Design:**

One hundred twenty cases (60 males) of volunteer patients with mild and moderate depression will be randomly divided into transcutaneous vagus nerve stimulation group (tVNS) and sham tVNS group. The treatment period lasts 4 months and all clinical and physiological measurements are acquired at the beginning and the end of the treatment period.

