## Methods and design

### Trial design

This study is a randomized, multicenter, double blind clinical trial with two treatment groups (tVNS and sham tVNS). Please see flow chart (Figure 1) for more details regarding the clinical procedures. The clinical endpoints are assessed by blinded independent observers. The central randomization system is used to assign patients to the tVNS or sham tVNS treatment groups. All procedures are performed by the Clinical Evaluation Center at the China Academy of Chinese Medical Sciences (CACMS) in Beijing. The Ethics committee of Institute of Acupuncture and Moxibustion, CACMS approved the experiment procedure.

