### Setting

Investigators are conducting the trial in four hospitals in Beijing, China. These four hospitals are: Guang An Men Hospital, China Academy of Chinese Medical Sciences; Huguosi TCM Hospital, Beijing University of TCM; Acupuncture Hospital, China Academy of Chinese Medical Sciences.

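### The primary response test is unadjusted although the supporting model adjusts for baseline HAM-D, and centre is in no stated analysis: a modest loss of precision and consistency, with no bias shown

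*Protocol article*

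**What the plan says.** All places are in the protocol article.

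- **Statistical analysis, primary outcome:** "Response rates across the two groups will be compared with the chi square" test. No strata or covariates are named.
- **Statistical analysis, supporting model:** post-treatment HAM-D-24 is regressed on treatment, and "covariances will include pre-treatment HAM score, age and gender". The section then adds: "Similar analyses will also be performed in other clinical and physiological outcome measurements". Hospital is not listed.
- **Trial design:** "This study is a randomized, multicenter, double blind clinical trial with two treatment groups". Allocation is described only as follows: "The central randomization system is used to assign patients to the tVNS or sham tVNS treatment groups". Stratification by hospital is not mentioned.
- **Setting:** "Investigators are conducting the trial in four hospitals in Beijing, China". The list that follows names three.
- **Sample size:** 39% response on tVNS, a difference of 25 points to be detected, 60 per group, 20% dropout, chi-square test at 0.05, 80% power.

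**The concern.** The sponsor already judges baseline severity, age and sex worth adjusting for when HAM-D-24 is analysed as a score. For the dichotomised version of the same scale, which is the primary outcome and carries less information, it adjusts for nothing. If the two analyses disagree, a reader cannot tell whether dichotomising or adjusting is the reason.

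The sample size leaves no spare power, so precision available from a baseline value already collected has some worth. Hospital is a natural source of variation in a multicentre trial, and it enters neither analysis. The article names the primary test, the supporting model and that model's covariates, so these are stated choices and not gaps left open for a later document.

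**Working it through.** **1. The plan's own figure.** The inputs from the Sample size section are p1 = 0.39, p2 = 0.39 - 0.25 = 0.14, and evaluable n = 60 x 0.8 = 48 per arm. Two-sided alpha of 0.05 is my assumption, as sidedness is not stated. The mean rate is (0.39 + 0.14)/2 = 0.265.

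- SE under the null = sqrt(2 x 0.265 x 0.735 / 48) = 0.0901
- SE under the alternative = sqrt((0.39 x 0.61 + 0.14 x 0.86) / 48) = 0.0864
- Power = Phi[(0.25 - 1.96 x 0.0901) / 0.0864] = Phi(0.850) = 80.2%

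Solving for 80% power gives n = 48 per arm, and 48/0.8 = 60. The stated figure is reproduced. Exact power of the uncorrected chi-square is 81.4%.

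**2. Room for covariates.** Expected responders = 48 x 0.39 + 48 x 0.14 = 18.7 + 6.7 = 25.4. A logistic model with treatment, baseline, age, sex and three centre terms has seven slopes, so 25.4/7 = 3.6 responders per slope. With treatment and baseline only, it is 25.4/2 = 12.7.

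**3. Centre alone.** This is a simulation with 20,000 runs per scenario, 48 evaluable per arm and four equal centres. It compares the chi-square with a Cochran-Mantel-Haenszel (CMH) test by centre. The between-centre SD on the logit scale is assumed.

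| Arms within centre | Centre SD | Power, chi-square | Power, CMH | Null error, chi-square | Null error, CMH |
|---|---|---|---|---|---|
| balanced | 0 | 81.4% | 81.3% | 5.5% | 5.4% |
| balanced | 0.5 | 81.9% | 82.4% | 4.8% | 5.0% |
| balanced | 1.0 | 82.5% | 85.0% | 4.0% | 5.0% |
| not balanced | 0 | 81.1% | 79.5% | 5.1% | 5.1% |
| not balanced | 0.5 | 81.3% | 81.1% | 4.8% | 4.7% |
| not balanced | 1.0 | 80.6% | 83.2% | 5.0% | 4.8% |

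The change in power runs from 79.5 - 81.1 = -1.6 to 83.2 - 80.6 = +2.6 points. The chi-square's error rate stays near 5%. It falls to about 4% only when arms are balanced within centre and centres differ strongly.

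**4. Baseline HAM-D-24 alone.** This simulation has 48 per arm, 39% v 14%, and logistic regression on treatment and baseline. The share of latent response variance explained by baseline (R2) is assumed.

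| Assumed R2 | Gain in power over chi-square |
|---|---|
| 0 | none (81% v 81%) |
| 0.1 | about 3 points |
| 0.2 | about 4 points |
| 0.3 | about 6 points |

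Null error was 4.8-5.8% for this model and 4.5-5.2% for the chi-square.

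**5. The seven-slope model.** Null error was 5.4-6.7% over several sets of runs, and 5.9-7.2% when both arms respond at 14%. Its gains at higher R2 (to about 88% at R2 = 0.3) are therefore partly those of a liberal test.

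**The case against.** The strongest defence is that nothing here is invalid. Under randomisation the chi-square holds its error rate, it is the test on which the trial was powered, and it reproduces the stated power. Chance imbalance is already allowed for in its 5% error. All of that stands, and it limits the point to efficiency and consistency.

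The gain is also uncertain. The article gives no prognostic strength for baseline, and response is already a percentage fall from each patient's own baseline, so strong residual dependence cannot be presumed. This stands too, which is why the gain is given as a range starting at zero. At zero, however, the baseline-only model lost nothing.

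A reader might infer more than the article supports:

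- **Bias, inflated error or a wrong sample size.** The working shows none of these.
- **An analysis that ignores its stratification factors.** No stratification is stated, so that argument is not available.
- **Different raters and operators by hospital.** This is not documented. Trial design says that blinded independent observers assess the endpoints, and places all procedures with one evaluation centre.
- **A sex quota that the test ignores.** The abstract says "One hundred twenty cases (60 males"), but no quota or stratum is described.
- **A need for every covariate in the primary model.** With about 25 responders, that makes the test mildly liberal.

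A fuller protocol or analysis plan could add centre. As the article stands, it lists the covariates without it.

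**Conclusion.** The point holds as a modest weakness. The primary comparison makes no use of a baseline measurement that the supporting model already adjusts for, and centre is in no stated analysis.

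The likely cost is about 0 to 6 points of power for an assumed baseline R2 of 0 to 0.3. For centre alone, the effect is between a loss of 1.6 and a gain of 2.6 points, for an assumed centre SD of 0 to 1.0 and four equal centres. These figures rest on 48 evaluable per arm, 39% v 14% response and a two-sided test. The case for change is that the adjustment is nearly free and already accepted by the sponsor elsewhere. The planned test would not mislead.

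**What to change.** Set the following before unblinding.

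1. **Primary test:** logistic regression of response on treatment and baseline HAM-D-24, with a test that is safe in small samples. Report the standardised (marginal) response difference with a 95% CI, which keeps the result on the scale used for the power calculation.
2. **Sensitivity analysis:** the unadjusted chi-square as now planned.
3. **Continuous models:** add centre to the HAM-D-24 regression and to the matching analyses of the other outcomes, where there is room for the extra terms.
4. **Centre factor:** first reconcile the four hospitals stated in Setting with the three named, and fix a rule for pooling small centres.

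The cost is revised analysis wording and slightly more analysis work. No new data are needed, and the sample size can stay. The risk to avoid is loading the logistic model: age, sex and centre need not all enter it.

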### Data safety monitoring

Independent data safety monitoring board members will meet every 6 months or as needed. Participants who show persistent worsening symptoms during the course of a clinical trial or develop unstable psychiatric symptoms (e.g., suicidality, homicidality, psychosis) will be withdrawn from the study and will be referred for appropriate treatment immediately.

According to the following classifications, a safety monitoring board will review and rate adverse events to determine whether to suspend the test condition.

Level 1: Security, without any adverse reactions.

Level 2: Safe, and have mild adverse reaction, do not need any treatment can continue to treatment.

Level 3: There are security issues; there is a moderate adverse reaction, after treatment may continue to treatment.

Level 4: Because of adverse reactions, terminate this research.

All adverse events will be reported to the Human Research Committee promptly in accordance with guidelines.

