### Choice of endpoints

All endpoints are measured at week 0 and week 10. The endpoints include the 24-item Hamilton Depression Rating Scale (HAM-D-24), the 17-item Hamilton Depression Rating Scale (HAM-D-17), Self-rating Anxiety Scale (SAS), Self-rating Depression Scale (SDS), electrocardiogram rate, breathing rate, and skin conduction response. Similar to previous studies [12,13], the primary outcome is the categorical classification of treatment response. We are interested in comparing the difference in treatment response rate between the two groups as measured by HAM-D-24, where treatment response is defined as a 50% or greater reduction in HAM-D-24 scores following a 10-week treatment.

In addition, previous studies [14-17] suggest that expectations for symptom relief can significantly influence the response to medications, acupuncture, and placebo. Thus, before the first treatment, patients are asked to rate on a scale how much they expect the treatment will relieve their symptoms, from “complete relief” to “do not work at all”.

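### Patients who worsen leave the study with no scheduled primary outcome, and the stated power holds only with dropouts left out; the plan should fix how they count in the response comparison

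*Protocol article*

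**What the plan says.** Four provisions of the protocol article bear on this.

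- **Data safety monitoring.** Participants whose symptoms keep worsening, or who become psychiatrically unstable, "will be withdrawn from the study and will be referred for appropriate treatment immediately". They leave the study, not only the stimulation.
- **Choice of endpoints.** "All endpoints are measured at week 0 and week 10". No other rating is scheduled.
- **Sample size.** The outcome is binary: "we define the treatment response as a 50% or greater reduction in HAM-D-24 scores following treatments". The pilot response rate on tVNS is 39%. The power statement reads "assuming a 20% dropout rate, with 60 patient in each group, we will have 80% power", for a difference of 25 points, with a chi-square test at the 0.05 level.
- **Statistical analysis.** "Response rates across the two groups will be compared with the chi square" test. The section names no analysis set and gives no rule for patients without a week-10 score.

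**The concern.** The trigger for withdrawal is worsening of the condition that the primary endpoint measures, so the loss of data is related to the outcome. A patient withdrawn at, say, week 5 has a baseline HAM-D-24 and no scheduled later one, and a 50% reduction cannot be computed unless a rule assigns the result.

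If such patients simply drop out of the denominator, the observed response rate rises in both arms, and it rises more in the arm that loses more of them. If tVNS works, fewer tVNS patients should meet the worsening criterion. More failures would then be removed from the sham arm, and part of the benefit would be hidden. An imbalance the other way would exaggerate a benefit or create one.

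**Working it through.** **Inputs.** From Sample size: response on tVNS p1 = 0.39, difference 0.25, 60 per arm, 20% dropout, α = 0.05 (taken as two-sided). The sham rate is not stated; I derive p2 = 0.39 − 0.25 = 0.14. Evaluable per arm: 60 × 0.8 = 48.

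**1. The plan's own figure.** Pooled-variance normal approximation:

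power = Φ{ [ |p1 − p2| − 1.96·√(2·p̄(1 − p̄)/n) ] / √( [p1(1 − p1) + p2(1 − p2)]/n ) }, with p̄ = (0.39 + 0.14)/2 = 0.265.

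- n = 48: (0.25 − 1.96 × 0.0901)/0.0864 = 0.850, so power is 80.2%. Exact enumeration of the Pearson chi-square gives 81.4%.
- n = 60: (0.25 − 1.96 × 0.0806)/0.0773 = 1.191, so power is 88.3% (exact 89.4%).

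The stated 80% therefore describes a comparison of 48 against 48.

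**2. Error rate with no true effect.** Assumptions: 25% response among all randomised in both arms, every dropout a failure, dropouts left out. The completer rate is 0.25/(1 − w), where w is the dropout proportion. The rejection rate is the sum of the two binomial probabilities over all tables with chi-square above 3.84.

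| Dropout by arm | Completers | Completer rates | Type I error |
|---|---|---|---|
| 20% / 20% | 48 / 48 | 31.2% / 31.2% | 5.2% |
| 25% / 15% | 45 / 51 | 33.3% / 29.4% | 7.2% |
| 30% / 10% | 42 / 54 | 35.7% / 27.8% | 12.9% |

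If only 5 of the 20 points are failure-related, with the same 3:1 imbalance (7.5%/2.5%), and the other 15 points are unrelated to outcome, the completer rates are 0.25/0.925 = 27.0% and 0.25/0.975 = 25.6%. With 47 and 50 completers (60 × 0.775 and 60 × 0.825, rounded), type I error is about 5.5%.

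**3. With a true effect.** Assumptions: 39% against 14% among all randomised, every dropout a failure. The reference is exact power of 89.4% on 60 per arm.

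| Dropout tVNS / sham | Completer rates | Observed difference | Exact power |
|---|---|---|---|
| 20% / 20% | 48.8% / 17.5% | 31.2 points | 92% |
| 15% / 25% | 45.9% / 18.7% | 27.2 points | 83% |
| 10% / 30% | 43.3% / 20.0% | 23.3 points | 69% |
| 30% / 10% | 55.7% / 15.6% | 40.2 points | 99% |

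Equal loss leaves the test level near 5% but turns a true 25-point difference into about 31 points.

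**4. Power when all 60 per arm are analysed.**

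- If 39% and 14% are completer rates and all dropouts count as non-responders: 0.39 × 0.8 = 31.2% and 0.14 × 0.8 = 11.2%. Power is 77.1% (exact 78.5%), and 80% would need 65 per arm.
- If 39% and 14% are rates in all randomised: 88.3% (exact 89.4%).

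**The case against.** A reader might infer that withdrawn patients have no outcome measured and that the primary test is therefore a completer analysis which drops treatment failures. The documents do not support that as fact:

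- The article gives the scheduled ratings. It does not say that a rating at withdrawal is ruled out.
- Statistical analysis names no analysis set. It does not say completers, and a fuller protocol or SAP, not shown, may analyse all randomised patients. An article's silence on this is not in itself an error.
- Dividing 48 by 0.8 to reach 60 is routine inflation for dropout. Trials that analyse everyone do it too, so it does not settle who is analysed.
- The 20% is dropout for any reason. The share due to worsening is not given. Severe depression and suicidal thoughts are excluded at entry, which gives no ground for equating the two.
- No rule in the article labels these patients as treatment failures. Response is defined only by the HAM-D-24 reduction.
- The 12.9% error and the 69% power need a threefold imbalance and every dropout to be a failure.

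All of this stands, and it limits the claim. It does not remove what the article does state: a withdrawal rule tied to the outcome, applied to the study as a whole, beside a schedule with one post-baseline rating and a power figure that counts 48 of 60. If the full plan does analyse all randomised patients, the published 80% does not describe that analysis and needs restating.

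**Conclusion.** The point holds in limited form. As written, patients withdrawn for worsening or instability have no scheduled primary outcome, for a reason related to that outcome. The power figure is consistent with leaving dropouts out of the chi-square, but does not prove it.

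The possible harm ranges from negligible to material. Type I error lies between 5.2% and 12.9% in the scenarios where every dropout is a failure, and is about 5.5% where only a quarter of them are. With equal 20% loss the level is intact, but 39% against 14% would appear as 48.8% against 17.5%. These results rest on assumed splits, an assumed 25% null rate and a derived 14% sham rate; the article gives no dropout by arm or by reason. The correction is worth making because it is cheap and removes the dependence on those unknowns for this group of patients.

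**What to change.** Leave the clinical withdrawal rule unchanged and amend the analysis and data collection:

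1. Define the primary analysis set as all randomised patients, in the arm to which they were assigned.
2. In the primary chi-square, count patients withdrawn under the worsening or unstable-symptom rule as non-responders, and state how other dropouts are classified.
3. Seek a HAM-D-24 rating at withdrawal, and still seek the week-10 rating.
4. Keep the completer chi-square as a sensitivity analysis.
5. Restate power on 60 per arm and say what the 39% and 14% refer to: about 77–78% if they are completer rates and all dropouts count as non-responders, about 88–89% if they are rates in all randomised.

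The cost is a change of wording, one extra rating at withdrawal and possibly a slightly lower stated power. Trial status reports 49 of the planned 120 recruited at submission, so the rule could be fixed before unblinding.

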## Discussions

Depression, with serious medical, social and economic consequences, represents a significant burden to both patients and society. Unfortunately, reports suggest that despite the progress that has been made in pharmacologic and psychological treatments, many MDD patients only partially benefit or do not benefit at all [1,3]. Additionally, pharmacologic treatments often have a high rate of relapse and intolerable side effects, which further the call for new treatment of MDD.

VNS is a relatively new FDA-approved somatic treatment for depressive disorders [1,4-6] and may provide long-term sustained benefits [1,5,7]. The limitations and adverse events related to VNS are quite obvious, including the involvement of surgery, perioperative risks, and potentially significant side effects such as hoarseness, throat pain, coughing, dyspnea, paresthesia, and muscle. Thus, VNS treatment is limited only to those patients who have exhausted the standard somatic treatments for MDD due to intolerance or lack of response [8].

The underlying mechanism of antidepressant action using VNS is not fully understood. Hypotheses are based on the anatomy and function of the vagus nerve, which is implicated in mood control [19]. It is known that the vagus nerve is a mixed nerve composed of about 80% afferent fibers. It is speculated that antidepressant effects of VNS are attributed partially to the projection of afferent fibers to the nucleus tractus solitaries, which is further connected directly and indirectly with brain structures including reticular formation in the medulla, parabrachial nucleus, the locus coeruleus, the amygdala, hypothalamus, insula, thalamus, orbitofrontal cortex, and other limbic regions responsible for mood and anxiety regulation [5,9].

This clinical trial aims to overcome these limitations by introducing a novel method of stimulating superficial branches of the vagus nerve to treat MDD. The evidence supporting the feasibility of this trial includes: 1) two proofs of concept, non-controlled, clinical trials demonstrated that tVNS can be used as an effective treatment for treatment-resistant MDD in both senior patients [18] and in epilepsy patients [20], another important indication of the VNS; 2) An fMRI study [21] showed that tVNS at specific ear regions can produce significant fMRI signal decreases, which is similar to the brain activity changes produced by VNS [22-24]. It is important to note that the same stimulation at ear regions without vagal supply could not evoke similar fMRI signal changes. In addition, only after tVNS, psychometric assessment of research subjects revealed significant improvement in well-being; and 3) two animal studies [25,26] demonstrated that stimulation of the certain areas of the ear with vagus nerve supplies can evoke firing of the vagus nerve and produce relatively specific physiological changes (e.g. decreased arterial pressure, heart rate, and intragastric pressure). Thus, results from both human and animal studies have endorsed the rational of the treatments.

In a previous study in senior patients with resistant MDD, Xu and colleagues [18] found that compared with the drug only group, drug plus electroacupuncture stimulation at a point in the ear where the vagus nerve is distributed can produce greater HAM-D score reduction and more good responders. However, the lack of an accepted control group significantly limited the interpretation of the study. In this protocol, we have included an active control group (sham tVNS), and used a double-blinded design, which could significantly enhance the quality of the clinical trial.

Compared with traditional VNS, tVNS has the advantage of being low cost, safe and non-invasive. Thus, it can be used on patients with mild to moderate MDD. If this study is successful, the results will significantly extend the application of VNS treatment to MDD and other disorders (including epilepsy, bipolar disorder, and morbid obesity) and will result in direct benefit to the patients suffering from these highly prevalent disorders.

Additionally, we believe that this study will also enhance our understanding of acupuncture mechanisms. As an important branch of acupuncture treatment and with extensive application in past decades, auricular acupuncture, with specific indication of different ear acupoints, remains a mystery. The tVNS treatment for MDD provides a unique angle as well as a model to investigate the biological basis underlying acupoint specificity.

Finally, to blind both the investigator and patient, we applied two pairs of carbon-impregnated silicone electrodes, only one of which was wired to give electrical output; thus, neither patients nor physicians know whether they received real or sham tVNS. This double-blinded design can significantly improve the quality of the trial and will shed new light on the development of methodologies in clinical trials of acupuncture treatment.

In summary, in this clinical trial, we are evaluating the efficacy of tVNS in mild and moderate MDD patients using a randomized and double-blinded design. The success of the trial will significantly improve the application of this promising new method.

